### Cost-effectiveness planes and cost-effectiveness acceptability curves

To deal with the uncertainty in the sampling distribution of the incremental cost-effectiveness ratio, resampling techniques with bootstrapping will be used. Replications will be done in each of the imputed databases and then combined. A minimum of 5,000 replications will be generated. Bias-corrected and accelerated (BCa) confidence intervals will be estimated on each of the imputed databases and then averaged [41]. Bootstrapped pairs of cost and effect differences will be plotted on cost-effectiveness planes and used to construct the cost-effectiveness acceptability curves.

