## Background

Major depressive disorder (MDD) generates high expenditure that is caused largely by its high prevalence, its recurrence and chronicity and because it usually affects young people of working age [1,2]. The social cost of this mental disorder is also very high, given the risk of suicide and the serious negative impacts in social, occupational and family situations [3]. From the work carried out by Goldberg and Huxley in the eighties, it is widely recognized that major depression is mainly treated at the primary care level [4]. More recent studies indicate that 10% to 16% of primary care patients fulfill criteria for a diagnosis of MDD [5,6]. It is therefore important that general practitioners (GPs) be capable of detecting and treating MDD using evidence-based medicine and taking the particularities of the primary level of care into account.

Psychotropic drugs, mostly antidepressants and anxiolytics, are highly prescribed in primary care in our setting as they are the standard treatment for MDD. About 70% of patients with a mood disorder receive psychotropic drugs in Catalan primary care [7]. Moreover, almost 25% of patients who do not fulfil criteria for a mood or anxiety disorder are also prescribed a psychotropic drug [7]. This percentage could include patients with minor depression or psychological distress that the GP misdiagnosed [8,9]. A review showed that benefits of antidepressants depend on the severity of the depressive episode, which may be minimal in patients with mild to moderate symptoms [10]. Another review showed that brief psychological therapy (brief cognitive behavioral therapy (CBT), counselling and problem solving therapy) were effective treatments in primary care for patients with anxiety, depression and mixed mental health problems [11]. The recommendations of the clinical practice guidelines for the treatment of MDD vary according to the severity of the case. The guidelines recommend medication for patients with moderate and severe depression and active monitoring (or watchful waiting) and referral for further assessment and interventions for those with mild to moderate symptoms [12,13].

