### Incremental cost-effectiveness ratios calculation

Incremental effects and costs between groups will be modelled using generalized linear models. First, different distribution families and link functions will be tested and Akaike and Bayesian information criterion (AIC and BIC) will be used to decide the model that best fits the distribution of the effects (QALYs and severity of depression) and costs. Second, to select adjustment variables, socio-demographic and baseline clinical variables considered to be relevant will be tested in the models using likelihood ratio tests. All the models will be adjusted for gender, age and the propensity score. Difference in costs and effects will be calculated using the final models in each of the imputed databases and combined as per Rubin’s rules [40]. Incremental cost-effectiveness ratios will be calculated by diving the difference in costs between groups by the difference in effects.

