### Sample size

In cost-effectiveness studies, sample size calculations have been criticized and their usefulness has been questioned [42]. This calculation is influenced by many parameters, some of them related to costs, which must be specified a priori. However, knowledge about costs and deviations is scarce so it is required to make assumptions that affect the calculation of the sample size. Moreover, this calculation requires to decide, in advance, what the maximum acceptable incremental cost-effectiveness ratio or maximum willingness to pay will be. Again, where to put the cutoff points for these parameters is a complicated decision. Finally, it should be borne in mind that the results of the economic evaluation will be presented in cost-effectiveness acceptability curves. These curves are not based on statistical inference so the meaning of sample size calculations could be questioned again.

On the other hand, to deal with the uncertainty in the sampling distribution of the incremental cost-effectiveness ratio, it will be necessary to perform resampling techniques that require a minimum sample size. Previous experience in these randomized studies with naturalistic conditions indicates that a total of 150 patients per arm will suffice [41,43].

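### A BCa bootstrap interval for the ICER can cover well below its nominal level, and has no clear reading, when the effect difference is small relative to its standard error

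*Protocol article*

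**What the plan says.** The section on calculating the ratios defines the quantity: "Incremental cost-effectiveness ratios will be calculated by diving the difference in costs between groups by the difference in effects". Cost and effect differences come from separate generalized linear models fitted in each imputed data set. Under Outcomes and participant timeline, the primary outcome is this ratio in two forms: cost per improvement in depression severity and cost per QALY.

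The section on cost-effectiveness planes and acceptability curves gives the purpose of the bootstrap: "To deal with the uncertainty in the sampling distribution of the incremental cost-effectiveness ratio, resampling techniques with bootstrapping will be used". On its size it says: "A minimum of 5,000 replications will be generated". On intervals it says: "Bias-corrected and accelerated (BCa) confidence intervals will be estimated on each of the imputed databases and then averaged". That sentence does not name the quantity the interval is for and gives no confidence level. The section closes with: "Bootstrapped pairs of cost and effect differences will be plotted on cost-effectiveness planes and used to construct the cost-effectiveness acceptability curves".

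The Sample size section says that "the results of the economic evaluation will be presented in cost-effectiveness acceptability curves" and adds: "These curves are not based on statistical inference so the meaning of sample size calculations could be questioned again". Net benefit is not mentioned anywhere.

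**The concern.** The only quantity named as the object of the bootstrap is the ICER, so the BCa interval is most naturally an interval for that ratio. BCa ranks the replicates of a single number and adjusts the percentiles for bias and skewness. That works when the number varies smoothly and its order means something. The ICER meets neither condition when the effect difference can fall on either side of zero. A negative ratio is either the best quadrant of the plane or the worst; a positive ratio is either dearer and better or cheaper and worse. As the effect difference passes through zero, the ratio jumps between plus and minus infinity.

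The Background makes this situation plausible. It cites a review showing that "benefits of antidepressants depend on the severity of the depressive episode, which may be minimal in patients with mild to moderate symptoms". What is at stake is the interval printed beside a primary outcome. It could exclude the true ratio much more often than its label says, and it could be hard to square with the acceptability curve drawn from the same replicates.

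**Working it through.** **No figure to reproduce.** The article gives no confidence level, effect size, standard deviation or willingness-to-pay value, and it supports 150 per arm by previous experience, without a formula. From the article come the ICER definition, the BCa method and n = 150 per arm. Everything else below is assumed.

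**1. Ordering (no assumptions needed).** Cheaper by 500 and better by 0.02: -500/0.02 = -25,000. Dearer by 500 and worse by 0.02: 500/(-0.02) = -25,000. The ratio alone cannot separate the two.

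**2. Scale.** For two arms of 150, SE of the effect difference = SD × √(2/150) = 0.1155 SD. With an assumed QALY SD of 0.20, SE = 0.0231.

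**3. Coverage.** Assumptions: bivariate normal data, QALY SD 0.20, cost SD 3,000, correlation -0.2, true cost difference -500 or +500, threshold 30,000 per QALY, nominal 95%, complete data, no covariates. There were 1,000 trials per scenario with 1,500 bootstrap replicates each and jackknife acceleration. Monte Carlo error is about 0.7 to 1.6 points. Net benefit = threshold × effect difference - cost difference. Paired entries are for cost differences of -500 and +500.

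| True effect difference (QALY) | In SE | In SD | ICER, BCa | ICER, plain percentile | Net benefit, BCa | Replicates with opposite effect sign to the estimate |
|---|---|---|---|---|---|---|
| 0.002 | 0.09 | 0.01 | 40 / 40% | 48 / 47% | 95.1 / 94.5% | 25 / 25% |
| 0.01 | 0.43 | 0.05 | 58 / 60% | 94 / 94% | 95.1 / 94.6% | 24 / 23% |
| 0.02 | 0.87 | 0.10 | 75 / 72% | 98 / 97% | 94.2 / 94.5% | 20 / 20% |
| 0.03 | 1.30 | 0.15 | 85 / 81% | 98 / 98% | 92.7 / 95.9% | 14 / 15% |
| 0.05 | 2.17 | 0.25 | 94 / 94% | 98 / 97% | 93.9 / 94.5% | 6 / 5% |
| 0.08 | 3.46 | 0.40 | 96 / 96% | 96 / 96% | 94.2 / 94.0% | 1 / 1% |

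BCa on the ratio falls well short up to about 1.3 SE (1.30 × 0.1155 = 0.15 SD) and recovers by about 2 SE. Between 0.43 and 1.30 SE the plain percentile interval does not undercover, so there the shortfall comes from applying the BCa corrections to a discontinuous ratio. The ordering problem in step 1 applies to both kinds of interval.

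**4. Other assumptions.** With skewed (gamma) costs of mean and SD 4,000, QALY SD 0.15 to 0.20, thresholds of 20,000 to 30,000, true net benefit of zero and QALY differences of 0.005 to 0.02 in either direction, the SE is 0.0173 to 0.0231. These differences therefore span 0.005/0.0231 = 0.22 to 0.02/0.0173 = 1.16 SE. The BCa interval for the ICER excluded the true ratio in 18% to 36% of trials (coverage 64% to 82%). The net-benefit percentile interval excluded its true value in 3% to 7%. A further run at 150 per arm gave ICER coverage of 73% to 83% at 0.2 to 1.2 SE and 92% to 95% from about 2 SE. The size of the shortfall depends on the assumptions; its location does not change much.

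**The case against.** The target is inferred. The article models the cost and effect differences separately and bootstraps them as pairs, so BCa intervals for those differences are a possible reading, and under it the problem disappears. This stands as a caveat. It does not settle the matter, because the section opens with the sampling distribution of the ratio and names no other target.

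A reader might infer that the interval is the plan's test of cost-effectiveness, and that it would miss a real advantage of active monitoring. The documents do not support this. No section gives the interval that role, and the Sample size section says results are presented in acceptability curves. At each threshold, such a curve shows the share of replicates with positive net benefit, so much of the decision information is already planned and sound. Any comparison of power would need a decision rule that the plan does not have.

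A reader might also infer that the interval will undercover in this trial. That is conditional on the true effect difference, and the article gives nothing to place the trial on the scale above. The Background does not point one way. It cites one economic evaluation with no cost-effectiveness difference, one in which adding an SSRI to supportive care was more cost-effective, and a study in older patients in which a problem-solving therapy did less well than paroxetine. A difference near zero is plausible, not predicted.

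Finally, only QALYs were simulated. Converting SE to SD units needs only n and applies equally to PHQ-9, but the exact coverage for the PHQ-9 ratio would also depend on the joint distribution with costs.

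**Conclusion.** The point holds in conditional form. If the BCa interval is for the ICER, as the text most naturally reads, it mixes opposite conclusions whenever replicates fall on both sides of zero effect. Its coverage was then about 40% to 85% for true effect differences below about 1.3 SE (roughly 0.15 SD at 150 per arm) and close to nominal from about 2 SE. These figures assume particular distributions, complete data, no covariate adjustment and a 95% level. The ordering defect rests on no assumption. The harm is confined to the reported ICER interval: the ICER point estimate, the cost-effectiveness plane and the acceptability curves do not depend on it. Because the ICER is the primary outcome and a small effect difference is plausible, the wording should be changed.

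**What to change.** In the section on cost-effectiveness planes and acceptability curves:

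- State which quantity the bootstrap interval is for, and its confidence level.
- Report intervals for the cost difference, the effect difference and incremental net benefit, from the same models and replicates, for QALYs and for PHQ-9. Use the threshold range of the corresponding acceptability curve, so that no further willingness-to-pay value is needed.
- Pool these intervals so that between-imputation variance is included. Averaging limits leaves it out: with many imputations and a normal approximation, coverage is that of ±1.96 × √(1 - f), where f is the fraction of missing information. This gives 93.7% at f = 0.1, 89.9% at 0.3 and 83.4% at 0.5 (assumed values of f). Without this change, the net-benefit interval would inherit a separate shortfall.
- Keep the ICER as a point estimate. Where replicates fall on both sides of zero effect, give the percentage in each quadrant instead of an ICER interval.
- Fix in advance what share of replicates across zero triggers that rule. Even at 3.46 SE about 0.8% crossed, or some 40 of 5,000, so a literal reading would almost always apply. The coverage of an ICER interval reported only when this rule allows it has not been checked.

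The cost is a change of wording and a few lines of code on replicates already planned, with no new data. The small downside is that readers who expect an ICER interval will sometimes not get one.

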### Missing data

Missing data patterns will be evaluated to assess if it is plausible that data is missing at random [39]. To minimize bias resulting from the loss of information not following a completely at random reason, missing values will be imputed using multiple imputation by chained equations. The imputation model will include relevant socio-demographic and prognostic variables associated with the drop-outs and outcome variables and variables to be included in the final cost-effectiveness models [40].

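### Averaging BCa limits over the imputed datasets leaves out the between-imputation variance, so these intervals are too narrow for their nominal level

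*Protocol article*

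**What the plan says.** Four statements in the protocol article's statistical analysis text bear on this point.

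- **Missing data:** "missing values will be imputed using multiple imputation by chained equations". The number of imputations and the expected missing rate are not given.
- **Incremental cost-effectiveness ratios calculation:** "Difference in costs and effects will be calculated using the final models in each of the imputed databases and combined as per Rubin’s rules".
- **Cost-effectiveness planes and cost-effectiveness acceptability curves**, on the replicates: "Replications will be done in each of the imputed databases and then combined", with the number set by "A minimum of 5,000 replications will be generated". The resulting pairs of differences feed the plane and the curves.
- **The same section**, on intervals: "Bias-corrected and accelerated (BCa) confidence intervals will be estimated on each of the imputed databases and then averaged".

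The last sentence names neither a confidence level nor the quantity the interval is for. The section opens by referring to the sampling distribution of the incremental cost-effectiveness ratio (ICER).

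**The concern.** Multiple imputation yields two sources of variance: sampling variance within a completed dataset, and variation of the estimate between completed datasets. The second expresses what is not known about the missing values. A bootstrap inside one completed dataset resamples imputed values as though they had been measured, so its interval reflects only the first source. The mean of several such intervals still reflects only the first.

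The plan would then treat uncertainty in two ways. The cost and effect differences are combined by a rule that adds the between-imputation variance, while the BCa intervals are combined by a rule that does not. Where both describe the same difference, the BCa interval will be the narrower, for no reason other than the omitted term.

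Cost-effectiveness is the primary outcome, and costs and QALYs are built up from visits at six and 12 months. A missed visit leaves a patient's 12-month total incomplete, so imputation will enter these quantities directly.

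**Working it through.** No figure in the protocol depends on this point, so there is none to reproduce. The check is on the rule itself.

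**Inputs from the protocol:** multiple imputation by chained equations; BCa limits per imputed dataset, averaged; Rubin's rules for the differences; 150 patients per arm (section on sample size).

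**Assumptions, because the protocol gives no value:** nominal level 95%; between-imputation share of variance from 5% to 50%; for the simulation, M = 10 imputations and 10% to 40% of outcomes missing.

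**1. Formula.** Let W be the mean within-imputation variance, B the variance of the estimates between imputations, and M the number of imputations. Rubin's total variance is T = W + (1 + 1/M)B. Averaging M lower and M upper limits gives an interval whose width is the mean of the M widths, so its half-width is about z√W. The BCa adjustment shifts limits for bias and skewness; it does not add B. With λ = (1 + 1/M)B/T:

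- width ratio = √(W/T) = √(1 − λ)
- coverage = 2Φ(1.96·√(1 − λ)) − 1

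Example, λ = 0.20: √0.80 = 0.894; 1.96 × 0.894 = 1.753; coverage 92.0%.

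| λ | Width relative to correct | Coverage of nominal 95% |
|---|---|---|
| 0.05 | 0.975 | 94.4% |
| 0.10 | 0.949 | 93.7% |
| 0.20 | 0.894 | 92.0% |
| 0.30 | 0.837 | 89.9% |
| 0.40 | 0.775 | 87.1% |
| 0.50 | 0.707 | 83.4% |

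**2. Simulation with actual BCa intervals.** Set-up: 150 per arm; difference in means of a normal outcome with SD 1; one covariate with correlation 0.4; outcomes missing completely at random; proper normal imputation with M = 10; 500 bootstrap replicates per dataset; 700 runs per setting.

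| Missing | Coverage: averaged BCa | Coverage: Rubin | Coverage: percentiles of pooled replicates | Width: averaged BCa | Width: Rubin |
|---|---|---|---|---|---|
| 10% | 93.6% | 94.9% | 94.7% | 0.446 | 0.473 |
| 20% | 92.1% | 94.1% | 94.0% | 0.446 | 0.502 |
| 30% | 87.0% | 93.7% | 92.6% | 0.448 | 0.542 |
| 40% | 84.7% | 93.7% | 92.9% | 0.447 | 0.588 |

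The simulation error is about √(0.95 × 0.05/700) = 0.8 percentage points near 95%, and √(0.87 × 0.13/700) = 1.3 points near 87%.

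**3. Reading.** The averaged width does not move as data are lost. It stays close to the width for complete data, 2 × 1.96 × √(2/150) = 0.453, as though no value were missing. The Rubin width grows from 0.473 to 0.588.

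**4. Plane and curves.** Replicates pooled over the M datasets have variance of about W + ((M − 1)/M)B. With M = 10 this is W + 0.9B against W + 1.1B under Rubin's rules. Most of the between-imputation variance is kept, which matches the coverage of 92.6% to 94.7% for the pooled-replicate percentiles.

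**The case against.** The strongest reply is that little rests on these intervals. The section on sample size says the results will be presented as acceptability curves; those curves and the plane come from combined replicates, and the cost and effect differences are combined by Rubin's rules. This stands, and it limits the point to the BCa intervals. A reader might infer that the whole uncertainty analysis is too precise. The documents do not support that.

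Second, the size is unknown. λ is not the drop-out rate. The imputation model is to include prognostic variables, and psychotropic medication use is also taken from pharmacy records, so λ could be small. The simulation used one covariate of modest strength. This also stands: at λ of 5% to 10% the loss is about half to just over one percentage point. A reader might infer that coverage below 90% is to be expected, but nothing in the protocol fixes where in the range the trial will fall. Nor does the protocol state 95%; it is the conventional level assumed here. The direction of the error is the same at any level.

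Third, a reader might go further and call the interval meaningless, because a ratio has no stable limits when the effect difference is near zero. The sentence on BCa intervals does not name its target, and the calculations above concern a difference, not a ratio. The Background cites an earlier economic evaluation with no difference in cost-effectiveness, which is not the same as no difference in effect, and it also cites studies that did find differences. The stronger claim is therefore not established and is not needed here.

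The interval sentence cites a reference for the method, which could not be consulted. The arithmetic does not depend on it.

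**Conclusion.** The rule is wrong as written. It is stated in the text, so it is not a detail left to a fuller plan, and no other section repairs it. Whenever values are imputed, the averaged BCa intervals are narrower than their nominal level requires, and they conflict with the Rubin combination of the cost and effect differences.

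The shortfall is negligible near λ = 5% and material from about λ = 20%, where the width is 0.89 of what it should be. These figures rest on an assumed 95% level, an approximately normal estimate and an assumed range for λ.

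**What to change.** In the section on planes and acceptability curves, replace the averaging step. Take the bootstrap variance of the cost difference and of the effect difference within each imputed dataset, pool each by T = W + (1 + 1/M)B, and form the interval with a t reference. State the confidence level, the number of imputations and the quantities for which intervals are given.

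There are two alternatives:

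- **Bootstrap first, then impute within each resample.** This carries both sources of variance but means running the imputation for every replicate.
- **Take percentiles of the replicates pooled over all imputed datasets.** The plan already generates these. This is much better than averaging but slightly below nominal at high missingness (92.6% and 92.9% at 30% and 40% missing in the simulation above).

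Reporting net monetary benefit as well would be a preference, not part of this repair.

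The cost is a changed sentence and minor programming, with no new data. Reported intervals become somewhat wider. The Rubin interval is symmetric and so gives up the skewness adjustment of BCa; if that matters for costs, the first alternative is the one to consider.

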### Sensitivity analyses

At minimum, the following sensitivity analyses will be performed: 1) an analysis from the healthcare perspective; 2) a per protocol analysis; 3) an analysis using the mean average salary instead of the minimum average salary for productivity losses; 4) an analysis not adjusted for the propensity score; 5) an analysis including only the patients that fulfill DSM-IV criteria for MDD.

